
### Monitoring

Trial conduct will be closely monitored by the MM and HNP teams to ensure strict compliance with data management and promote study quality. We do not anticipate any risks to the subjects, but any adverse events will be noted.

## Discussion

This study, which builds on our previous work, will demonstrate the effectiveness of the Million Marker endocrine disrupting chemical (EDC) exposure report-back on increased EDC environmental health literacy (EHL), readiness to reduce exposures (i.e. readiness to change, RtC), and exposure reduction itself, in EDC-tested individuals. Additionally, we hypothesize that providing further intervention beyond report-back (i.e. EDC-specific environmental health literacy education and community support) will be a measurable improvement over report-back alone, in terms of EDC EHL and exposure reduction behavior, a reduction in individual exposures, and an improvement in clinical biomarkers.

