### Previous work

In previous work, [44] participants in the Healthy Nevada Project completed EHL and readiness to change surveys before (*n* = 424) and after (*n *= 174) an EDC exposure report-back intervention (measured via the MM mail-in testing kit). Report-back of results included urinary levels, information about health effects, sources of exposure, and personalized recommendations to reduce exposure. Participants ranged in age from 18-61, were primarily women (75%), and white (79%). EHL was generally very high at baseline. Higher EHL knowledge was shown among older participants (*p* = 0.02) and those self-rated in poorer health (*p *= 0.007). EHL behaviors increased after report-back (*p *= 0.003).

For readiness to change, 72% were already or planning to change their behaviors. Women were generally in earlier stages than men (p=0.071), but post-intervention, women increased their readiness (p=0.053), while men decreased (p=0.007). When asked what challenges they faced in reducing exposure, 79% cited not knowing what to do. This dropped to 35% after report-back. Participants with higher propylparaben were younger (p=0.03), women and participants who rated themselves in better health had higher levels of some phthalates (p=0.02-0.003 and p=0.001-0.003 respectively). After report-back, monobutyl phthalate decreased among the 55 participants who submitted a second urine test (p<0.001). Of the 50 participants who completed final surveys, 50% reported now using non-toxic personal products, 44% were using non-toxic household products, 20% dined out less, 32% ate less packaged food, 40% used less plastic, and 48% read product labels more.

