## Methods

### Study design

This study is an ongoing collaboration between Million Marker and the Healthy Nevada Project (MM-HNP Study). We will test and compare the effectiveness of 1) EDC exposure report-back (control), and  2) a self-directed online interactive curriculum of EDC EHL material, with access to live coaches and an online forum (intervention). We hypothesize that the self-directed online interactive curriculum with personalized and community support will be more effective (superior) than EDC report-back alone at reducing EDC exposures (behavior change and metabolite concentrations), as well as increasing EDC-specific EHL, readiness to reduce exposures, and well-being. These two arms will be tested in a longitudinal EDC randomized control trial (n=600). Participants will be allocated to intervention groups by the MM team via block randomization, using random-number generation software. The HNP team will generate the allocation sequence and enroll participants. Outcomes for this aim will measure surveyed changes pre- post-interventions in EDC EHL, including EDC-specific knowledge/behavior/attitudes, RtC, well-being, and urine EDC metabolite concentrations. Additionally, we will test a subset of individuals from each intervention arm (*N* = 150 from each group, for a total of
*N* = 300) for clinical biomarkers using a mail-in blood card test. Outcome assessors and data analysts will be blinded to the intervention status of the participants. Additionally, participants will not be aware of their intervention status (i.e. what the other group undergoes).

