**Fig. 1 Fig1:**
[figure not shown]
Timeline of study events for control and intervention groups

Participants will be able to view the results of their Lifestyle Audit online, as well as their test results and reports. These tools will also help participants to self-monitor their behaviors and exposure reduction progress. All participants (control and intervention) will receive a report back of their urinary exposure levels. The control group will receive a list of general recommendations for exposure reduction based on their EDC exposure levels,while the intervention group will receive a more personalized exposure reduction plan based on the information collected in their Lifestyle Audit.

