We will test 150 individuals in each treatment group (i.e. report-back only group (control) vs. the intervention group (treatment)) for a total of N=300. Sample size estimates were based on a systematic review and meta-analysis of low-fat diets and testosterone measurements in men [74]. Effect sizes across six studies ranged from 0.26-0.7 with an average of 0.37. For a two-tailed paired-samples t-test measuring free testosterone, with an alpha of 0.05 and 95% power to detect an effect of 0.37, a sample size of 97 is required. Multiplying by 1.3 to account for attrition, we arrive at 126 per group. With two groups the total comes to 252 participants. Thus, our sample of 150 participants per group should be sufficient to detect an effect of this size.

We hypothesize that, along with the decrease in EDC exposure, individuals will exhibit improved health biomarkers after EDC report-back. Additionally, we posit that individuals receiving the treatment (i.e. online curriculum, coaching, and community forum support), will show both increased EDC reduction and improved health biomarker levels compared to the control (report-back only) group.

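### Both arms receive report-back, so the trial can test the whole intervention package against report-back with general advice, but cannot demonstrate that report-back works or credit a difference to education and community support alone

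*Protocol article*

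**What the plan says.** The Discussion makes two statements. The first is that the study "will demonstrate the effectiveness of the Million Marker endocrine disrupting chemical (EDC) exposure report-back on increased EDC environmental health literacy (EHL", followed by readiness to change and exposure reduction. The second is a hypothesis that "providing further intervention beyond report-back (i.e. EDC-specific environmental health literacy education and community support) will be a measurable improvement over report-back alone".

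Study design labels the comparator "EDC exposure report-back (control", in brackets. Intervention design adds: "All participants (control and intervention) will receive a report back of their urinary exposure levels". The reports are not the same, however. "The control group will receive a list of general recommendations for exposure reduction based on their EDC exposure levels", while the intervention arm gets a plan personalised from a Lifestyle Audit. The test-kit section and the data collection section say the same, and the kit section shows that controls skip the audit call.

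The before-after reading of report-back recurs elsewhere. Clinical biomarker testing hypothesises that "individuals will exhibit improved health biomarkers after EDC report-back" and sizes the subset with a paired, within-group test. Expected outcomes and limitations anticipates a significant fall in both arms, larger in the intervention arm.

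**The concern.** Showing that report-back works needs people who did not receive it, and this trial has none. Randomisation therefore says nothing about report-back itself, and a significant fall in both arms could be published as proof of something the design cannot show. This is foreseeable: Previous work already counts a before-after fall in one phthalate metabolite, among 55 people who gave a second sample, as evidence that report-back succeeded.

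The second statement has a narrower problem. It describes the added intervention as education and community support, but the arms differ in more than that. If the intervention arm does better, the personalised plan could be the reason. The earlier service already offered this element: "Report-back of results included urinary levels, information about health effects, sources of exposure, and personalized recommendations to reduce exposure".

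The protocol ties its results to FDA approval, insurance coverage and marketing, so what may be concluded matters.

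**Working it through.** **1. What differs between the arms, and where it is named.**

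| Component | Control | Intervention | Named as part of the intervention in |
|---|---|---|---|
| Urinary levels reported back | yes | yes | not a contrast |
| Recommendations | generalised | personalised plan | not in Study design, Clinical biomarker testing or Discussion |
| Lifestyle Audit call | no | yes | not in any of the three |
| 8-week curriculum | no | yes | all three |
| Coaching | no | yes | Study design, Clinical biomarker testing |
| Forum | no | yes | all three (as community support in the Discussion) |

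The first row has no contrast, so no between-arm analysis can estimate the effect of report-back. The second and third rows are contrasts that the Discussion's gloss, "providing further intervention beyond report-back (i.e. EDC-specific environmental health literacy education and community support", leaves out.

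**2. The plan's own figure.** Clinical biomarker testing gives 97 for a two-tailed paired t-test with effect 0.37, alpha 0.05 and power 95%. The normal approximation is ((1.960 + 1.645)/0.37)² = 94.9. The exact noncentral-t calculation gives n = 97 with power 0.950. Then 97 × 1.3 = 126.1, the stated 126. The figure reproduces, but it sizes a within-group change, which is the uncontrolled quantity.

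**3. What a within-arm test would show with no report-back effect.** From Sample size: 300 × 0.5 = 150 completers per arm. The drift is my assumption, as the protocol gives none. For drift d, in SDs of the change, the paired t-test has noncentrality d × √150:

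| Assumed drift (SD of change) | Chance of p < 0.05 |
|---|---|
| 0 | 5% |
| 0.1 | 23% |
| 0.2 | 68% |
| 0.3 | 95% |

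To put this on a concentration scale, assume a log SD of 1.0 at each test and a pre-post correlation of 0.4. The SD of log change is √(1 + 1 − 2 × 0.4) = 1.095. A 20% shift is ln(1/0.80) = 0.223, so d = 0.223/1.095 = 0.204, and 0.204 × √150 = 2.50. By the normal approximation, power is Φ(2.50 − 1.96) = 0.70. With correlation 0.2 the SD is 1.265 and the figure is 0.58; with 0.6 the SD is 0.894 and the figure is 0.86.

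These figures do not show that drift will occur. They show that the test cannot tell drift from effect.

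**4. The between-arm contrast.** Drift common to both arms cancels in the difference. If an effect of 0.37 is assumed on the between-arm scale, 150 per arm gives Φ(0.37 × √(150/2) − 1.96) = Φ(1.24) = 0.89. With 150/1.3 ≈ 115 per arm it gives about 0.80. The rewording proposed here does not by itself call for a larger sample.

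**The case against.** The case for the protocol is substantial.

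- **The randomised comparison is sound for what it compares.** The arms are randomised, both reports are openly described, and the analysis section plans a between-arm regression of change. A reader might infer that neither Discussion statement can be supported at all. That goes too far: package versus report-back with general advice is a valid contrast, and only attribution to named components fails, as in any multicomponent trial.
- **Much of the package is declared.** Report-back and curriculum lists tailored report-back among six programme components, and the Study design hypothesis refers to personalised as well as community support. The second Discussion statement is a hypothesis, and no passage credits the curriculum alone. This stands. What remains is that the audit and the personalised plan are missing from three places that define the intervention.
- **The biomarker statement is also a hypothesis**, within work the protocol calls exploratory. True, but it still concerns change without a comparator.
- **Generalised advice for controls is a disclosed choice.** That the earlier service was personalised does not make this comparator an error.

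Two specific sources of drift might also be inferred, and the documents do not establish either. One is a single September-to-December seasonal shift: September 2024 is only the first of several staggered waves, and oxybenzone, the sunscreen filter, is one of 13 analytes. The other is a laboratory batch shift between tests: the protocol promises single-batch analysis per instrument setup and labelled surrogates. The 2-4 week turnaround sits awkwardly with that promise, but the point does not depend on it.

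**Conclusion.** The concern holds in two parts.

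First, the claim to demonstrate the effectiveness of report-back is one this design cannot support. This follows from the arm descriptions alone and needs no numerical assumption. The alternative explanations are general ones: time trends, repeated surveys and testing, selective dropout at the planned 50%, and regression to the mean, for example if people with high first results are more likely to return. Expected outcomes and limitations itself notes that participants may begin reducing exposure on joining; it expects bias towards the null, but a before-after reading would count such change as a report-back effect. The 23% to 95% range is illustrative and rests on assumed drift of 0.1 to 0.3 SD.

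Second, the arm difference estimates the effect of the whole package against report-back with generalised recommendations. It does not isolate education and community support. The documents do not support the stronger reading that the randomised comparison is uninformative.

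The matter is one of claims and definitions, of moderate importance, and should be settled before results are reported.

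**What to change.** - State one confirmatory comparison: the between-arm difference for the full package (curriculum, coaching, forum, Lifestyle Audit and personalised plan) versus report-back with generalised recommendations.
- In the Discussion, remove the promise to demonstrate the effectiveness of report-back.
- Report within-arm changes, including the report-back expectations in Clinical biomarker testing and in Expected outcomes and limitations, as descriptive estimates with confidence intervals and no claim of effect.
- Name the Lifestyle Audit and the personalised plan in the intervention definition in Study design, Clinical biomarker testing and Discussion.
- Word any positive result as the effect of the package.

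This changes text only: no extra participants, procedures or measurements. The price is that the claim of efficacy for report-back itself is given up.

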### The need for EDC exposure reduction intervention

In order to mitigate the health impacts and corresponding financial burden of exposures to EDCs, individuals must have access to an affordable, easy, and rapid way to test their exposures to EDCs. Additionally, improving the environmental health literacy (EHL) of individuals is imperative for them to understand *how* to reduce these exposures. Environmental health literacy (EHL) is the knowledge of harmful environmental exposures and how they affect health [66, 77, 78]. Although environmental exposure (exposome) contributes 70% to chronic disease risk, [79] EHL is low in the general population [77] and among healthcare providers [80–82]. To address this, the National Institutes of Health (NIH) has called for increased EHL research, including methods to increase EHL, [77] and for applications (RFAs) of EHL research [83]. Thus, the Million Marker (MM) EDC testing kit and service is a major step in allowing the public to “learn what’s inside” of them and take action to reduce their personal exposures. The MM test kit is a non-invasive (i.e. urine), affordable, and scalable personalized environmental exposure testing and analysis service, followed by a tailored intervention program to empower individuals to optimize their health, prevent diseases, and manage existing conditions.

### Previous work and current protocol

In previous work, we developed and tested the first mobile EDC intervention service (exposure report-back and personalized recommendations via mobile app) for its efficacy in reducing EDC levels, increasing EHL, increasing readiness to reduce exposures (i.e. readiness to change, RtC), and assessing system usability among reproductive-age participants recruited from the Healthy Nevada Project (HNP), one of the largest population health cohorts in the world. We found decreased EDC exposure with the intervention, as well as increased RtC in women (but, interestingly, a decrease in RtC in men) [44]. However, participants had difficulty carrying out the intervention on their own. Because of the difficulty in the EHL subject matter, participants still felt ill-prepared to apply their knowledge to making healthier lifestyle changes and cited financial reasons and limited choices as barriers to change [44]. Therefore, in the current study, we will address these perceived limitations by testing a self-directed online interactive curriculum with live counseling sessions and individualized support modeled after the highly effective Diabetes Prevention Program (DPP) [84] and Omada Health [63] (which provides a digital interactive DPP).

The at-home Million Marker testing and report-back service, along with the online curriculum, will provide an easy-to-use roadmap for individuals and communities to reduce personal exposures and optimize health. Additionally, it allows for scalable, economical, and far-reaching exposomic population research and intervention studies, with opportunities for industry, academic, and government partnerships.

### Trial status

Recruitment of HNP participants to this study beganJuly 2024, with subjects being recruited into study waves with staggered starts for ease of recruitment and data collection. The initiation of study events began as the first wave of participants was recruited, September 2024.

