### Need for EDC intervention

Endocrine-disrupting chemicals (EDCs), including bisphenols, phthalates, parabens, and oxybenzone, are present in over 90% of the population at any one time, [5, 6] and have been linked with numerous health effects in laboratory and human studies, including breast cancer, [7, 8] obesity, [9–11] metabolic syndrome, [12] diabetes, [13] and infertility, [14, 15] and effects on the fetus that can manifest later in life, including cancers, IQ loss, neurotoxicity, attention-deficit hyperactivity disorder, childhood obesity, adult obesity, type 2 diabetes, cardiovascular and metabolic disease, genital defects, infertility, pregnancy complications, and mortality from reduced testosterone [4, 7, 9–11, 16–25].

BPA is used to make polycarbonate plastic and epoxy resins and is found in numerous consumer products (e.g. thermal receipts, plastic foodware, can linings). BPA is a known hormone disruptor and has been linked to numerous health effects in laboratory animals [23] and chronic diseases and disorders in humans, including infertility, cardiovascular and metabolic disease, asthma, and child development [16]. It has also been deemed a mammary carcinogen [24]. Due to these health concerns, BPA has been increasingly replaced with other bisphenols (BPs), which are structurally or functionally similar to BPA, (such as BPS and BPF) and share many of the same health concerns as BPA [26–29]. Phthalates are used as to make plastic flexible and are added to fragrances to disperse scent [30]. Phthalates are also hormone disruptors; they have long been known for antiandrogenic effects (i.e. decreased anogenital distance in infant boys) [31–33]. Phthalate exposure is also associated with infertility, type 2 diabetes, asthma, and other health problems [34]. Parabens are a group of chemicals widely used as antimicrobial preservatives in personal care products and packaged food. Parabens are hormone disruptors, showing estrogenic and antiandrogenic activity, as well as blocking aromatase. Exposure has been linked to adrenal and thyroid disruption, metabolic changes, developmental-behavioral changes in animals, [35] and reduced fertility in humans [36]. Oxybenzone is a UV filter that is found in many sunscreens, hair products, cosmetics, and lotions [37, 38]. Oxybenzone is an EDC—it has been shown to be proliferative in estrogen-responsive cancer cell assays, [38, 39] as well as promoting the growth of androgen-dependent prostate cancer cells [40].

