### Intervention design

Upon consenting and randomization, all participants will be sent baseline surveys and test kits (for baseline urinary exposure levels, and, for a subset, clinical biomarkers). The control group (n = 300) will complete post-test surveys and use the second kits approximately 3 months after the baseline assessment, while the intervention group (n = 300) will complete a Lifestyle Audit and engage in the 8-week curriculum described above. The intervention group will submit the kits 2 weeks after completion of the curriculum (i.e. 3 months after the baseline test). See Fig. 1 for the control vs. intervention group study events.

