### Surveys, study measurements and secondary outcomes

EDC levels will be measured at baseline and 3 months. Participants' age, level of education, income, BMI, self-assessed health status, smoking status, alcohol intake, exposure to other toxic substances (e.g. dangerous chemicals, radiation), will be collected via questionnaires after recruitment to the study. We will measure participants’ environmental health literacy (EHL), readiness to change (i.e. readiness to reduce exposures, RtC), and well-being (general health, social support, financial well-being, sleep, stress, and physical activity) at baseline, 3 months (post-intervention surveys), and 6 months (exit surveys) after baseline (see Fig. 1). We will also assess usability and participant satisfaction 3 months after baseline (post-intervention). The EHL survey was adapted from the framework of the “general environmental health scale” section of the survey by Lichtveld et al. [66] which was validated in two geographic areas via exploratory and confirmatory factor analysis. Questions include those regarding individuals’ environmental health knowledge (e.g. “Household dust contains harmful chemicals”), attitudes (e.g. “I am concerned about chemicals I am exposed to through products I buy”), and behaviors (e.g. “I take steps to avoid inhaling cleaning products”). We adapted the RtC survey based on the Transtheoretical Model of Health Behavior Change [67] in which we ask about current efforts and interest in limiting exposure to harmful chemicals. EHL and RtC will be assessed to determine their association with EDC levels, as well as the effect of the intervention on EHL and RtC.

We will also measure participants’ well-being via relevant questions from three validated surveys. General health and sleep will be assessed using questions from the Behavioral Risk Factor Surveillance System; [68] stress will be measured via the Perceived Stress Scale (PSS), [69] and physical activity will be assessed using the International Physical Activity Questionnaire [70, 71]. These secondary health outcomes will be measured at baseline, 3-month and 6-months later to assess changes.

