After analyzing the samples, we will calculate the percentiles (25^th^, 50^th^, 75^th^ and 95^th^) of analyzed samples and compare participants’ levels for each of the metabolites with existing MM users, as well as the national averages derived from NHANES. Participants’ metabolite levels will be categorized into low (below 25^th^ percentile), medium (equal or above 25^th^ to 75^th^), high (equal or above 75^th^ to 95^th^), and very high (equal or above 95^th^). For the intervention group, MM will also audit their lifestyle behaviors and products used. Problematic areas, such as handling thermal receipts, consuming canned food or drinks, and using products with fragrance, the presence of other harmful ingredients, etc. will be listed in the report along with the lab results and comparisons. The MM team will also be blinded to participants' identifiable information to ensure no bias is introduced. A detailed list of personalized behavior and product recommendations will be provided to the participants for them to follow and make changes. The control group will receive generalized recommendations, based on their exposure levels, that cover multiple areas, including diet, home environment, personal and household products, etc. The same process will be performed for the second kits. EDC levels from participants at baseline (first test) and second test will be compared, and factors such as food, diet, product use, health status, and stress and physical activity levels will be correlated with changes in EDC exposures. Covariates, including sex, BMI, age, education level, household income, and social support will be included in the analysis.

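### Waves start at different times of year and are retested about 3 months later, but the stated adjustment has no wave or date term: season is confounded with pre-post change (most plausibly for benzophenone-3), while the randomised comparison loses only precision

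*Protocol article*

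**What the plan says.** **Calendar.** Trial status reports "subjects being recruited into study waves with staggered starts for ease of recruitment and data collection" and adds: "The initiation of study events began as the first wave of participants was recruited, September 2024". No later wave is dated.

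**Retest.** Surveys, study measurements and secondary outcomes: "EDC levels will be measured at baseline and 3 months". Under Intervention design, controls "use the second kits approximately 3 months after the baseline assessment". For the other arm: "The intervention group will submit the kits 2 weeks after completion of the curriculum (i.e. 3 months after the baseline test").

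**Analyte.** Need for EDC intervention: "Oxybenzone is a UV filter that is found in many sunscreens, hair products, cosmetics, and lotions". Benzophenone-3 (oxybenzone) is in the measured panel. The same section gives half-lives of 6 hours to 3 days for these chemicals, so a urine sample reflects current use.

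**Analysis.** Data collection, management, and analysis makes the pre-post difference per analyte, adjusted for specific gravity, the primary outcome. It says that "factors such as food, diet, product use, health status, and stress and physical activity levels will be correlated with changes in EDC exposures", and then: "Covariates, including sex, BMI, age, education level, household income, and social support will be included in the analysis". A second list in that section names BMI, age, gender, diet, education and household income. The between-arm regression controls for demographic variables found to be significant. None of these is wave, month or season.

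**Claims.** Study design states superiority of the curriculum over report-back alone. Expected outcomes and limitations also expects a significant fall after report-back and intervention, and the opening of the Discussion says that the study will demonstrate the effect of report-back on exposure. Both arms receive report-back (Intervention design).

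**The concern.** For any one wave, baseline and retest are about a season apart. The first wave runs from September to about December. If sunscreen use falls over those months, benzophenone-3 falls in both arms with no help from report-back or curriculum. The only bias that Expected outcomes and limitations discusses for exposure change is towards the null. An autumn-to-winter wave would push the other way.

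Two of the planned inferences have no protection from randomisation:

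- **Report-back lowers exposure.** With report-back in both arms, this rests wholly on change from baseline.
- **Behaviours correlate with exposure change.** This is observational. Factors such as physical activity or diet may shift with the season while the analyte also shifts, and pooling waves without a calendar term mixes the two.

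For the randomised comparison, the stake is efficiency.

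**Working it through.** **Inputs from the article.** 150 per arm after 50% attrition (Sample size); one retest at about 3 months; two-sided alpha 0.05. The article gives no figure on season and no SD for change in an analyte, so both are assumed over a range. The method can be checked against the one sample size the article works through (Clinical biomarker testing): a paired t-test with effect 0.37 and 95% power. The noncentral t gives 96.9, matching the stated 97.

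**1. Within-arm change, no treatment effect.** Let season multiply the geometric mean by r between the two samples, and let SD be the standard deviation of log change. The noncentrality is |ln r| / SD × √150. For r = 0.8 and SD = 1.0 this is 0.223 × 12.25 = 2.73, which gives 78%. Chance of a significant change:

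| Seasonal fall | SD 1.0 | SD 1.5 | SD 2.0 |
|---|---|---|---|
| 10% | 25% | 14% | 10% |
| 20% | 78% | 44% | 27% |
| 30% | 99% | 83% | 58% |
| 50% | 100% | 100% | 99% |

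This assumes that everyone shares the same seasonal shift, as in a September-to-December wave. With four equal waves spread evenly round the year (seasonal factor 1.5 or 2, SD 1.0 or 1.5), the average shift cancels and simulated within-arm rejection is 3–6%. The harm therefore depends on an unbalanced calendar.

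**2. What could produce such falls (illustration only).** If the share of recent sunscreen users drops from p1 to p2 and users have k times the level of non-users, the geometric mean falls by 1 − k^−(p1−p2). For 30% to 5% and k = 5, 10, 30, the fall is 33%, 44%, 57%. For 20% to 5% it is 21%, 29%, 40%. The shares and ratios are assumptions.

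**3. Between-arm comparison, no treatment effect.** Simulation with 2,000 runs, 150 per arm, one wave or four, seasonal factor 1.5 or 2, SD 1.0 or 1.5, with and without blocking inside waves:

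- Bias without a wave term is at most 0.006 log units, within simulation error of zero.
- Type I error is 3.0–5.7% without wave terms and 4.7–5.9% with them.

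**4. Precision between arms.** With four evenly spaced waves and seasonal factor f, wave adds (ln f)²/2 to the variance of log change. For f = 2 this is 0.693²/2 = 0.240. For a true difference of 0.33 SD, power is about Φ(0.33 × √75 / √(variance ratio) − 1.96). With wave modelled: Φ(2.858 − 1.96) = 82%.

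| SD | f | Variance ratio | Power without wave |
|---|---|---|---|
| 1.0 | 1.5 | 1.08 | 78% |
| 1.0 | 2 | 1.24 | 73% |
| 1.5 | 1.5 | 1.04 | 80% |
| 1.5 | 2 | 1.11 | 78% |

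**5. What a wave term can do.** In the arm comparison and the correlations, participants in the same wave differ in arm or behaviour, so a wave term removes the shared seasonal shift. In a within-arm test, season and time since baseline coincide inside each wave, so no wave term separates them.

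**The case against.** The strongest objection is that the main question is the superiority of one randomised arm over the other. Both arms share the calendar, so season drops out in expectation. That stands. A reader might infer that season distorts the trial's treatment comparison; the design and the simulation do not support this.

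A reader might also infer that arm balance by season is left to chance. It is not. Study design specifies block randomisation, and if blocks are filled in enrolment order, imbalance within a wave is limited to part-blocks at its edges. The article does not say that blocks are formed within waves, but blocking detail is normally kept elsewhere. Two routes remain by which some season could enter: differential dropout by wave, with 50% attrition expected, and retest dates tied to baseline in controls but to curriculum completion in the intervention arm. The article shows neither to be happening.

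The objection that covariates belong in the analysis plan has force. The checklist refers to an Appendix 2 that is not shown, and the first covariate list is open-ended. But the article does fix a rule for the arm regression, significant demographic variables, and wave is not one.

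On the correlations, a link between sunscreen use and benzophenone-3 would be genuine even if season drives the use. The confounding concerns other factors that move with season. Nor do these correlations underlie the advice given to participants: that rests on exposure levels, the Lifestyle Audit and earlier published evidence.

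Finally, the article lists hair products, cosmetics and lotions as further sources of oxybenzone, and only the first wave is dated. A spring-to-summer wave with the opposite shift is possible but not documented.

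**Conclusion.** The point holds in limited form. As the adjustment is stated, pre-post change is confounded with season, most plausibly for benzophenone-3. This weakens the uncontrolled claim about report-back and the behaviour correlations. If the waves cluster in one part of the year, even a 20% seasonal fall gives a false within-arm finding in 27–78% of trials for SDs of 2.0 down to 1.0; if they spread evenly over the year, the problem largely disappears.

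The randomised comparison is unbiased in expectation. Omitting wave costs it precision only: 4–24% more variance, and power of 73–80% against 82%, under seasonal factors of 1.5–2 and SDs of 1.0–1.5. Every seasonal size here is an assumption, and the omission is established only for the text of the article.

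**What to change.** 1. Add recruitment wave, or sample collection date, as a term in the between-arm regression for the analytes and in the analysis correlating behaviours with exposure change.
2. Form the randomisation blocks within each wave still to be recruited.
3. Base conclusions on the between-arm difference. Do not present within-arm falls, above all for benzophenone-3, as effects of report-back. Name season as a limitation of any pre-post result that is shown.

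The laboratory already reports the date each sample is received and shipping is overnight, so a close proxy for collection date exists. The article does not say that wave is recorded, so this should be confirmed.

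The cost is a few degrees of freedom, one randomisation setting, and a narrower claim about report-back alone.
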